#### Follow-up period: end of surgery to 24 h after surgery

2.8.3

NRS and RASS scores will be evaluated by a dedicated follow-up researcher at 30 min, 1 h, 6 h, and 24 h after surgery. CRBD grades and patient satisfaction scores will be recorded at the same postoperative time points. The researcher responsible for documentation will complete the CRF. Patients’ vital signs on admission to the PACU, intraoperative anesthetic agents, RASS, NRS, CRBD, and adverse events will be recorded in the electronic data system. The study timeline is presented in Table 1.

**Table 1 tab1:** Timetable of the study period.

Timepoint	Screening period (−2~−1 d)	Preparation period (−1~0 d)	Surgery period (0 d)	Follow-up period (after awakening until 24 h postoperatively)								
		T0		T1	T2	T3	T4	T5	T6	T7	T8	T9
Eligibility screen and informed consent	X											
General condition of the patient^a^	X											
Training^b^		X										
Vital signs^c^	X			X	X	X	X	X		X	X	X
Random allocation		X										
Hot compress												
The CRBD score						X				X	X	X
The NRS score						X				X	X	X
Adverse events record^d^												
Satisfaction of patients												

*T0, Before induction of anesthesia; T1, 10 min after awakening; T2, 20 min after awakening; T3, 30 min after awakening; T4, 40 min after awakening; T5, 50 min after awakening; T6, 1 h after awakening; T7, 6 h after awakening; T8, 12 h after awakening; T9, 24 h after awakening.

a Patients were educated about how to recognize CRBD (for example, suprapubic discomfort or burning with the urge to urinate) and how to distinguish them from surgical pain.

b Obtain the patient’s name, hospitalization number, age, medical history (whether there are the following conditions, serious heart, liver, kidney and other diseases; If the hot compress site has skin injury, ulcer, sensory disturbance, acute closed injury, suppurative infection or acute inflammation and other infectious diseases, skin diseases, severe diabetes, high fever and excessive use of product materials, it is not suitable for hot compress; Patients with prostatic hypertrophy, urethral stricture, and a history of indwelling catheter within 1 year.

c Blood pressure, heart rate, and oxygen saturation.

d Burns, redness, itching, allergies, etc.

To ensure strict compliance with the measurement time points, the study procedures were optimized. The follow-up researcher will perform assessments at the ward or PACU exactly at the scheduled times. Vital signs will be documented by nurses at fixed time points, and all data will be entered into the electronic system with time stamps to guarantee accuracy and consistency. All researchers and nurses received uniform training to standardize assessment procedures and minimize human-related time-point deviations.

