## Introduction

1

Similar to overactive bladder, catheter-related bladder discomfort (CRBD) is mainly characterized by a frequent and urgent need to urinate as well as a burning sensation in the suprapubic region in patients recovering from anesthesia who have an indwelling catheter (1). CRBD may cause anxiety and pain, increase the need for anesthetics, and increase the incidence of postoperative complications (2). CRBD is not only a risk factor for postoperative agitation but also induces postoperative delirium in severe cases (3). Postoperative CRBD is a well-known side effect of indwelling catheter placement that occurs in 47%–95% of inpatients. Preventing or reducing the severity of CRBD is helpful for improving patients’ quality of recovery and reducing the incidence of postoperative agitation (4).

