### Study design

2.1

This is a multicenter, randomized, parallel group controlled study. The study period is November 2024–November 2025. A 24-h observation period will be included in the study (pictured). Patients who provide written informed consent will be tentatively enrolled and screened for eligibility during the observation period. In the experimental group, a hot compress (40–45 °C) of a Xiao-Xu-Ming-Tang and salt mixture will be placed above the pubic symphysis immediately after intubation. In the control group, a hot compress (40–45 °C) of one-tenth of an improved Xiao-Xu-Ming-Tang (This dose was confirmed to be non-therapeutic for CRBD based on our pre-experimental data and clinical dosage principles, cannot produce a significant effect on relieving bladder discomfort) and sea salt mixture will be placed above the pubic symphysis. During the observation period, the severity of CRBD will be graded using a scoring system developed and used by Agarwal et al. (18). The severity of CRBD will be divided into 4 grades: grade 1, the patient reports no symptoms of urinary tract or bladder discomfort; grade 2, the patient reports mild urinary tract or bladder discomfort only after prompting; grade 3, the patient reports moderate urinary tract or bladder discomfort without prompting but does not exhibit any behavior alluding to the discomfort; and grade 4, the patient reports severe urinary tract or bladder discomfort. The behaviors alluding to discomfort included flailing limbs, a strong vocal response, and attempts to remove the catheter.

*Experimental group (Composition of the TCM formulation)*: 9 g Qianghuo, 9 g Chuanxiong, 9 g Huangqin, 6 g Mahuang, 9 g Muxiang, 9 g Prepared *Aconitum Carmichaelii* Radix, 6 g Fangji, 9 g Fangfeng, 6 g Yangchun Sha, 9 g Sheng Baishao (full dose of improved Xiao-Xu-Ming-Tang) are ground into powder, mixed thoroughly with 100 g coarse sea salt, packed into a breathable cloth bag, heated to 40–45 °C, and applied as a hot compress above the pubic symphysis immediately after intubation until 60 min after surgery.

*Control group*: one-tenth of the full dose of improved Xiao-Xu-Ming-Tang powder (the proportion of each medicinal material is consistent with the experimental group), mixed thoroughly with 100 g coarse sea salt, packed into a breathable cloth bag, heated to 40–45 °C, and applied as a hot compress above the pubic symphysis immediately after intubation until 60 min after surgery.

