#### Primary outcomes

2.2.1

The primary outcomes will be the incidences of moderate and severe CRBD (grades 3 and 4) at 30 min after surgery.

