### Randomization and masking

2.4

An envelope lottery will be used to randomize patients into groups, and because the study will be conducted across 3 centers, stratified randomization is required, with 30 patients included from each center, 15 of whom will be assigned to the experimental group and the remaining 15 will be included in the control group. The study will be conducted in double-blinded manner, and patients were only informed that they were enrolled in a clinical trial for the prevention of postoperative CRBD and were assigned to a study group with a unique study number, and the specific grouping (experimental/control) and the differences in the composition of the hot compress bags (full dose/one-tenth dose of medicinal powder) were not disclosed to the patients at any stage before, during, or after the surgery. The hot compress will be placed over the patient’s pubic symphysis immediately after intubation under general anesthesia and removed 60 min after surgery by a site nurse who will not be involved in follow-up visits. Patients, anesthesiologists, surgeons, note-takers, data registrars and analysts will be unaware of the group assignments. The TCM package will be distributed to each center by the Department of TCM of Shanghai Fourth People’s Hospital. Both groups will emit the smell of TCM, which are indistinguishable by odor alone. Group assignments will be maintained by the personnel at the main site who are not involved in the study but rather responsible for the study group numbers and hot compresses. Only when the patient has a serious adverse reaction that is suspected to be related to the intervention itself will he or she be responsible for the emergency unblinding of the patient to ensure timely treatment of the condition.

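### The hot compress is still on the suprapubic skin at the primary 30-minute CRBD reading, and patients are taught to separate CRBD from surgical pain but not from sensation under the compress

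*Protocol article*

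**What the plan says.** **Compress.** Protocol article, 2.1 (Study design), has the bag in both arms "applied as a hot compress above the pubic symphysis immediately after intubation until 60 min after surgery", at 40–45 °C with 100 g of sea salt. The arms differ only in herb dose, which is one-tenth in the control arm. Section 2.4 repeats that the bag is "removed 60 min after surgery by a site nurse who will not be involved in follow-up visits".

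**Primary reading.** Section 2.2.1 defines the primary outcome as "incidences of moderate and severe CRBD (grades 3 and 4) at 30 min after surgery". The first secondary outcome in 2.2.2 repeats the grading at 1, 6 and 24 hours. Table 1 counts from a different origin: its key reads "T3, 30 min after awakening".

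**What counts as CRBD.** The Introduction includes "a burning sensation in the suprapubic region in patients recovering from anesthesia" among the features. Table 1, footnote a, trains patients to recognise "suprapubic discomfort or burning with the urge to urinate"; the one competing source it names is surgical pain. The four grades in 2.1 all concern urinary tract or bladder discomfort, and grade 3 is moderate discomfort volunteered without a prompt.

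**Skin sensation.** The third secondary outcome in 2.2.2 counts scald, redness, pruritus and allergy above the pubic symphysis. Table 1, footnote d, lists similar events as adverse events.

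**The concern.** The outcome is a self-reported sensation, and the treatment can produce a sensation at the same place and at the same moment. The training in footnote a accepts that patients may confuse sources of discomfort, but the contrast it states leaves out the source that the trial itself adds.

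The setting makes confusion plausible. The Discussion describes patients in early recovery from anaesthesia as disoriented and more sensitive to pain, and it concedes that the main outcome is subjective. Footnote a can also be read in two ways: the urge to urinate may qualify both symptoms, or only the burning. On the second reading, suprapubic discomfort alone is taught as CRBD.

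If some patients without moderate or severe CRBD were graded 3 or 4 because of what they felt under the bag, the arms would look more alike than they are. Power would fall, and the number needed to treat promised in 2.7 would come out too large. The 6-hour and 24-hour grades do not have this problem because the bag is off by then.

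**Working it through.** **1. Timing**

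- On the end-of-surgery clock, the primary reading is at 30 minutes and removal at 60, so the bag is on with 30 minutes left. The 1-hour reading falls at the time of removal, and the text does not say which comes first.
- On the awakening clock of Table 1, let w be the minutes from end of surgery to awakening. T3 is then at w + 30 after surgery, and the bag is still on if w + 30 < 60, that is, if w < 30. The 1-hour reading (T6) is at w + 60, after removal whenever awakening follows the end of surgery.

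The primary reading is therefore taken under the bag on either clock, unless awakening comes 30 minutes or more after surgery. The position of the 1-hour reading depends on the clock.

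**2. The plan's own sample size (2.6)**

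Inputs: 70% versus 35%, two-sided α = 0.05, power 0.90, 1:1 allocation.

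n = [1.960 × √(2 × 0.525 × 0.475) + 1.282 × √(0.70 × 0.30 + 0.35 × 0.65)]² / 0.35²
= (1.384 + 0.848)² / 0.1225 ≈ 40.7, so 41 per arm.

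The plan states 42, which agrees to within one patient. Allowing for 5% loss, 42 / 0.95 = 44.2, so 45 per arm, as stated. Power at 42 per arm is 0.91.

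**3. Illustration of dilution**

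Let f be the share of patients without true grade 3–4 CRBD who are graded 3 or 4 because of compress sensation. The documents give no value, so f is assumed. True cases are assumed to stay cases. The observed rate is p + (1 − p)f. With the same f in both arms the difference becomes 0.35 × (1 − f).

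| f, both arms | Control | Full dose | Difference | Power at 42 per arm | n per arm for 90% power | NNT = 1/difference |
|---|---|---|---|---|---|---|
| 0 | 70.0% | 35.0% | 35.0 points | 0.91 | 41 | 2.9 |
| 5% | 71.5% | 38.3% | 33.3 points | 0.88 | 45 | 3.0 |
| 10% | 73.0% | 41.5% | 31.5 points | 0.84 | 50 | 3.2 |
| 20% | 76.0% | 48.0% | 28.0 points | 0.76 | 62 | 3.6 |

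Example, f = 10%: control 0.70 + 0.30 × 0.10 = 0.73; full dose 0.35 + 0.65 × 0.10 = 0.415; difference 0.315.

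If the true rates are equal, a common f leaves them equal, so it does not create a false positive result.

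**4. What could differ between arms**

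Only the herb dose differs. If it irritated the skin so that f were 10% in the full-dose arm and 0 in control, the rates would be 70% versus 41.5%, a difference of 28.5 points with power 0.76. Nothing in the documents supports that figure. It shows only the direction, which is against the experimental arm.

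**The case against.** The strongest reply is that the written scale already excludes skin sensation. A reader might infer that any suprapubic burning a patient volunteers becomes grade 3 whatever its source. Section 2.1 does not say that: every grade refers to urinary tract or bladder discomfort. Footnote a mentions the urge to urinate, and skin discomfort has its own outcome and adverse-event entry. This stands, and it is why protection is called partial. What remains is that the patient has to make the attribution, and the stated training covers one confusable source and not the other.

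Second, temperature, site, salt mass and duration are identical in the two arms, and 2.8.2 provides a temperature probe at the contact surface. This also stands. A reader might infer bias in favour of the herbs, but the design gives no route to it: shared heat dilutes, and herb irritation would count against the full dose. The Introduction adds that two herb doses were adjusted to limit pungency.

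Third, the article is condensed. Footnote a presents its symptoms as examples, 2.8.1 says patients are instructed beforehand to avoid confusion, and 2.1 describes centralised, assessed training of evaluators. A full training sheet may cover compress sensation. The point therefore rests on the contrast that footnote a does state, not on the absence of a script.

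Finally, a reading taken during treatment is not an error in itself. The protocol states its timing openly, and nothing in it makes an on-treatment endpoint invalid.

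**Conclusion.** The point holds as a modest measurement weakness of the primary endpoint that is cheap to repair. The timing overlap and the incomplete taught contrast are both in the text. The grade wording and the separate skin outcome limit the damage without removing it.

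The likely consequence is some loss of contrast. Under an assumed 5–10% false-positive share common to both arms, the loss is 1.7 to 3.5 points of the planned 35 (35 − 33.3 and 35 − 31.5), and 3 to 7 percentage points of power at 42 per arm. These figures rest on the planned rates of 70% and 35%, an assumed f, and no missed true cases. The documents do not allow f to be estimated. A larger loss through herb irritation is possible but unsupported by any figure in them.

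**What to change.** 1. Align footnote a and the assessor's script with the grade wording in 2.1, so that patients are taught to separate warmth, burning or itching of the skin under the compress from bladder or urethral discomfort with urge, as well as from surgical pain.
2. At 30 minutes and 1 hour, ask the already planned skin-discomfort item before the CRBD grade and record the two separately.
3. Take the 1-hour grade at the same point relative to removal in both arms, and say which point that is.
4. Reconcile the end-of-surgery clock in 2.2 with the awakening clock in Table 1.

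Section 2.1 gives a study period ending in November 2025, so enrolment may be complete. In that case items 1 to 3 can no longer be applied. The 30-minute result should then be reported as CRBD during application and checked against the 6-hour and 24-hour grades taken after removal. That check is supportive only, since discomfort may also change with time.

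The cost is a sentence in the training material, a fixed question order at two time points, and a slightly longer bedside assessment. No change to the compress schedule or dose is proposed.

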## Discussion

3

In this multicenter RCT, we will evaluate the effectiveness of an improved version of the TCM hot compress of improved Xiao-Xu-Ming-Tang in safely alleviating CRBD after surgery for ureteral calculi. This study will provide evidence of the efficacy of this innovative intervention in relieving CRBD and therefore improving patient satisfaction.

CRBD is highly prevalent worldwide (47%–95%). Its pathophysiology-M-cholinergic receptor-mediated involuntary contraction of bladder smooth muscle is consistent across populations (4). CRBD is mainly characterized by discomfort in the suprapubic region and a frequent and urgent need to urinate, with or without urinary incontinence. In the early stage of recovery from general anesthesia, patients are not fully conscious, are disoriented, have increased pain sensitivity, and are prone to CRBD (1, 19). But the core drawbacks of traditional preventive methods for CRBD lie in three key dimensions: limited efficacy, significant side effects, and poor compliance. Furthermore, most of these methods only address symptoms rather than the root causes, making it difficult to eradicate the risk fundamentally (20).

This discomfort is believed to be induced by involuntary bladder smooth muscle contractions mediated by muscarinic receptors. Medications such as ketamine, nefopam, dexmedetomidine, and tramadol are commonly used to manage CRBD (21–24). Additionally, transcutaneous electrical nerve stimulation, acupuncture, and pudendal block have also been reported to be effective in the prevention and treatment of CRBD (6, 25, 26). However, these management strategies can have various adverse effects, such as postoperative nausea and vomiting, dry mouth, headache, facial flushing, hypotension, blurred vision, seizure, muscle weakness, and pelvic floor muscle weakness. TCM is expected to prevent postoperative CRBD because of its safety, easy application and repeatability. Given its excellent safety profile, ease of administration, and reproducibility, TCM holds significant promise for preventing postoperative CRBD. Its implementation does not rely on intricate cultural or medical constructs, thereby facilitating its global adoption across diverse healthcare systems and regions. Furthermore, the hot compress procedure is highly standardized (with fixed temperature, site, and duration), enabling rapid proficiency among medical professionals from various professional backgrounds (15). In this study, the intervention will continue from the time of anesthesia induction to ensure a sustained effect. It can effectively reduce the incidence of complications after general anesthesia, shorten the length of PACU stay, and reduce the length of hospital stay.

Some limitations of this study should also be considered. Firstly, because the main outcome of this study is the incidence of moderate to severe CRBD, which is the subjective feeling of patients. To minimize confounding variables of patient factors on the trial, we strictly restricted the gender, age, type of surgery, and duration of anesthesia. Secondly, urethral catheterization was performed with a standard 18-Fr Foley catheter, thus comparisons of other sized catheters were not possible. Large-diameter Foley catheters are an independent risk factor for CRBD. In addition, we did not perform urine flow assays, residual urine analyses, or prostate size evaluations, possibly confounding the results.

## Conclusion

4

This multicenter, randomized, double-blind, controlled trial will provide high-quality clinical evidence on whether the improved Xiao-Xu-Ming-Tang traditional Chinese medicine hot compress offers a safe, non-invasive, and cost-effective strategy for preventing postoperative moderate–severe CRBD in patients undergoing transurethral ureteral laser lithotripsy under general anesthesia. If the intervention is proven effective, it will provide a new clinical option for the prevention of CRBD, especially for clinical settings that require low-cost and easy-to-operate interventions, and has the potential for wide clinical promotion worldwide.
